### Trial interventions

#### Cast treatment

Control treatment is non-operative with immobilisation in a below elbow cast for 6 to 10 weeks, followed by mobilisation. Pragmatically we have not specified whether the thumb should be included in the cast as this does not affect union rate [3], but we will record the type of cast used. Early Computerised Tomogram (CT) will be obtained at the discretion of the treating surgeon if plain radiographs at 6 to 12 weeks raise the suspicion of non-union which we expect in 10 to 12 % of non-operatively treated patients. If non-union is confirmed on radiographs and/or CT scan, urgent surgical fixation will be performed. The surgical procedure and post-operative care will be similar to the surgical arm of this trial. This is the current standard non-operative pathway [1].

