#### Rehabilitation

All patients randomised into the two groups will receive standardised, written physiotherapy advice detailing the exercises they need to perform for rehabilitation following their injury. All patients in both groups will be advised to move their shoulder, elbow and finger joints fully within the limits of their comfort. Those patients treated in a cast will perform range-of-movement exercises at the wrist as soon as their plaster cast is removed at the 6-week follow-up appointment if there are no concerns regarding bone union. Those patients who have the fracture fixed may begin wrist exercises as soon as comfort permits if they do not have a plaster cast or as soon as the cast is removed. In this pragmatic trial, any other rehabilitation input beyond the written information sheet (including a formal referral to physiotherapy) is at the discretion of the treating surgeon. However, a record of any additional rehabilitation input (type of input and number of additional appointments) is to be recorded at the 52 week follow-up.

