### Objective measures

We are measuring the range of movement [44] of both wrists using a goniometer and grip strength [45–48] of both hands using a calibrated Jamar dynamometer at baseline, 6, 12, 52 weeks and 5 years.

The measurements will be done with the subject seated, arm by the side, elbow bent at 90° and the wrist in neutral position for rotation [49]. The second setting on the Jamar dynamometer will usually be used but patients with large hands may need to use the third setting. This reflects common and evidence-based practice in assessing grip strength [50]. The Beighton Joint Laxity Score (excluding the thumb count for the injured wrist) will be recorded at baseline to measure hypermobility of joints [51]. These assessments will be standardised across participating sites using an instruction manual.

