### Statistical analysis plan

A detailed analysis plan will be agreed with the Data Monitoring and Ethics Committee at an early stage of the study, before all of the data has been collected. Any subsequent amendments will be clearly stated and justified. All analyses will be conducted on an intention to treat basis, including all available randomised participants in the groups to which they were allocated. Analyses will be conducted using 2-sided significance tests at the 5 % significance level (unless otherwise stated). The statistician conducting the analyses will remain blind to treatment group until all data summaries and results are finalised. For some variables the type of data reveals treatment allocation (e.g. complication data), hence relevant analyses will be conducted by a second statistician.

The flow of participants through each stage of the trial will be presented in a CONSORT flow diagram [57]. PRWE scores will be summarised descriptively (number, mean, standard deviation, median, interquartile range, minimum and maximum) at each time point by treatment group and overall. PRWE at baseline will be collected for the time before and after injury. Mean pre-injury PRWE scores will be presented in total and for each treatment group and compared descriptively to PRWE scores post-injury at baseline and all other follow-up time points.

Our primary analysis will compare total PRWE scores between treatment groups at 52 weeks using a covariance pattern mixed model incorporating all post-randomisation time points, where effects of interest and baseline covariates are specified as fixed effects, and the correlation of observations within patients over time (random effect) is modelled by a covariance structure. The outcome modelled will be PRWE at 6, 12, 26 and 52 weeks, predicted by treatment group, time, treatment group-by-time interaction and adjusting for age, fracture displacement (undisplaced vs. minimally displaced) and hand dominance. Estimates of the difference between treatment groups in total PRWE scores will be derived at all time points with 95 % confidence intervals and *p*-values. The primary end point will be the treatment effect estimate at 52 weeks. This model will naturally include all patients who provide data for the baseline covariates, and valid PRWE data for at least one post-randomisation follow-up time point.

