The impact of missing PRWE outcome data will be minimised to some extent by using the mixed model, which allows the inclusion of intermittent responders in the primary analysis. PRWE scores for complete and intermittent responders will be compared descriptively. The impact of missing data will additionally be assessed using multiple imputation by chained equations. Missing outcome and covariate data will be predicted by age, fracture displacement, hand dominance, available PRWE data at other follow-up time points, and any baseline covariates found to be predictive of missing 12 month outcome data.

All secondary outcomes will be summarised descriptively. The following outcomes will be analysed using the same methods as the primary analysis adjusting for the same covariates: pain and disability subscales of the PRWE, physical health and mental health component summaries of the SF-12 and range and grip strength. Where available, baseline values of the dependent variable will also be included as a covariate in the models. The presence of any complication assessed by clinical examination up to 52 weeks will be analysed by logistic regression (sufficient numbers permitting). Complications will be defined as medical, surgical or plaster cast related. Union will be assessed as a percentage (0–100 %) and categorised as: total non-union [0 %]; slight union [>0–20]; partial union [>20–70]; mostly united [>70–<100]; and complete union [100 %]. Summary statistics for union will be presented at each time point by trial arm. Union will be dichotomised into a ‘Probably need surgery’ group [0–20 %] and a ‘Probably do not need surgery’ group [>20–100 %] and analysed using a logistic regression adjusting for treatment group.

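### Range and grip are measured on both sides at baseline, but the stated model gives the uninjured side no role as a covariate; adding it is a free gain in precision on secondary outcomes, and the cast timing at the 6-week measurement needs reconciling.

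*Protocol article*

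**What the plan says.** The Objective measures section describes measuring movement "of both wrists using a goniometer and grip strength", the latter "of both hands using a calibrated Jamar dynamometer at baseline, 6, 12, 52 weeks and 5 years".

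The Statistical analysis plan section describes the primary mixed model as "adjusting for age, fracture displacement (undisplaced vs. minimally displaced) and hand dominance". The secondary outcomes to be analysed by the same method with the same covariates include "physical health and mental health component summaries of the SF-12 and range and grip strength". One outcome-specific covariate is added: "Where available, baseline values of the dependent variable will also be included as a covariate in the models". No section says whether the range or grip outcome is the injured side alone, a ratio to the other side or a difference between sides. None gives the uninjured-side measurement a role in the analysis.

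On timing, the Study participants section admits patients presenting within two weeks of injury, so baseline follows the fracture. Under Cast treatment: "Control treatment is non-operative with immobilisation in a below elbow cast for 6 to 10 weeks, followed by mobilisation". Rehabilitation has cast patients start wrist exercises "as soon as their plaster cast is removed at the 6-week follow-up appointment if there are no concerns regarding bone union". The same section foresees that some surgical patients will also have a cast.

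**The concern.** Recovery of wrist range and strength is part of the second trial objective (Table 1). People differ widely in normal grip and range, so a covariate that captures the patient's own normal makes the treatment contrast more precise. A baseline taken on an acutely fractured wrist is likely to reflect pain and guarding as much as normal function. The uninjured side is a more direct reference, and patients with a wrist fracture in the opposite limb are excluded. The trial collects that value, yet the stated covariate list does not use it.

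The second matter is the 6-week visit. The primary method produces between-group estimates at every time point, and range and grip are measured at 6 weeks. If some control patients are still in a cast then, their values may be missing, possibly because of concern about union. The article states no rule for them, and its missing-data text is written for the PRWE.

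**Working it through.** **The plan's own figure.** The only sample size stated is for the PRWE: a 6-point difference with SD 20, 80 % power and 2-sided 5 %. Per arm, n = 2 × (1.960 + 0.842)² / 0.3² = 174.4, rounded up to 175, so 350 in total; 350 / 0.8 = 437.5, so 438 randomised. Both figures reproduce. They say nothing about range or grip, and 175 per arm is used below only to express precision.

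**Precision: inputs.** The documents give no correlations, so all of these are assumed:
- r1, follow-up value with injured-side baseline: 0.3 (range 0.1 to 0.5)
- r2, follow-up value with uninjured-side baseline: 0.6 (range 0.4 to 0.8)
- r12, between the two baselines: 0.3 to 0.5

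**Formulas.** With the injured-side baseline only, R² = r1². With both baselines, R² = (r1² + r2² − 2·r1·r2·r12) / (1 − r12²). The standard error is proportional to √(1 − R²).

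**Middle case.**
- Injured side only: R² = 0.09, leaving 0.91 of the variance.
- Both, r12 = 0.3: R² = (0.09 + 0.36 − 0.108) / 0.91 = 0.376. SE ratio = √(0.624 / 0.91) = 0.83.
- Both, r12 = 0.5: R² = (0.09 + 0.36 − 0.18) / 0.75 = 0.36. SE ratio = √(0.64 / 0.91) = 0.84.
- Difference detectable at 80 % power with 175 per arm, 2.8016 × √(1 − R²) × √(2/175): 0.286 SD with the injured side only, 0.237 to 0.240 SD with both.

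**Extremes of the assumed range.**
- Largest gain (0.1, 0.8, 0.5): R² = 0.57 / 0.75 = 0.76. SE ratio = √(0.24 / 0.99) = 0.49.
- Smallest gain (0.5, 0.4, 0.5): R² = 0.21 / 0.75 = 0.28. SE ratio = √(0.72 / 0.75) = 0.98.

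These are single-time-point figures. They ignore whatever age and hand dominance already explain, and they take the injured side as the outcome.

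**The 6-week visit.** Cast treatment gives "immobilisation in a below elbow cast for 6 to 10 weeks, followed by mobilisation", so a patient may still be in a cast when range and grip are due at 6 weeks. Rehabilitation describes the cast coming off at that appointment, with a condition about union that can be read as applying to the removal or to the exercises. The two sections do not settle who can be measured at 6 weeks.

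If only measured patients counted, the cast-arm mean would look better by (share unmeasured) × (their shortfall). The documents supply neither input. Borrowing the expected 10 to 12 % non-union as the share and assuming a 0.5 SD shortfall gives 0.10 × 0.5 = 0.05 to 0.12 × 0.5 = 0.06 SD. Assuming 10 to 50 % unmeasured and 0.2 to 0.8 SD gives 0.02 to 0.40 SD. This is before the mixed model recovers anything from later visits, and with no unmeasured patients in the surgical arm.

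**The case against.** The strongest reply is that the article never says the injured side alone is analysed. Both sides are measured at every visit, which would also allow a ratio or a difference, and either would already bring in the patient's own normal. Defining the outcome by side is commonly left to the detailed analysis plan, which is not shown. This stands: a reader might infer that the plan adjusts only for the injured wrist, but the text does not establish it. What remains is that the covariates are stated, and the uninjured-side baseline is not named among them.

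A weaker covariate is also not an error. It causes no bias in a randomised comparison; it only forgoes precision. That stands too, and it is why this is an improvement rather than a defect.

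On the 6-week visit, a reader might infer that patients in a cast cannot be measured and that the contrast is therefore selective. The documents do not support that. Nothing says such patients cannot be measured, Rehabilitation describes removal at that very appointment, and surgical patients may be in casts as well. Patients with a missing 6-week value stay in the mixed model through their later visits, which is valid if data are missing at random. Selection is possible but unquantified.

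Dropping formal inference at 6 weeks would carry a real cost, because the benefit suggested for surgery is early recovery of function. That objection stands.

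**Conclusion.** The point holds as a no-cost improvement to secondary analyses. Both sides are measured at baseline, and the stated adjustment set leaves the uninjured side out. If the injured side is the outcome, adding that value would plausibly cut the standard error to about 0.83 to 0.84 of the planned model's, with 0.49 to 0.98 under wider assumptions, so the gain could be nearly nil. Every correlation is assumed. If the outcome is a ratio or a difference, these figures do not apply.

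A reader might also take 1 − r² alone and claim intervals at 80, 71 or 60 % of their width for r = 0.6, 0.7 or 0.8. Those figures compare with no baseline adjustment, not with the planned model.

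Separately, the two statements on cast timing leave the 6-week range and grip measurement unclear. This calls for reconciliation and transparent reporting; it does not show that the 6-week estimate is biased. The 52-week PRWE analysis and the sample size are unaffected.

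**What to change.** In the analysis of range and grip:
- State whether the outcome is the injured side, a ratio or a difference.
- Add the uninjured side's baseline value as a covariate in each range and grip model, alongside age, displacement, hand dominance and the baseline of the dependent variable.

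For the 6-week visit:
- Reconcile Cast treatment with Rehabilitation on whether patients may still be in a cast when range and grip are measured.
- Keep the formal 6-week estimate, report by arm the number still immobilised and not measured, and interpret the estimate in that light.

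The covariate change is wording only: the data are already collected, and the price is one further parameter per model. The 6-week report needs cast status and the reason for a missing measurement to be available for that visit. No formal test is given up.

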## Background

Scaphoid fracture is the most common carpal fracture and is an important public health problem as it predominantly affects young active individuals (mean age 29 years [1]) in their most productive working years. These fractures account for 2 to 7 % of all fractures [2]. However, 10 to 12 % do not unite when treated with plaster cast, with a higher incidence of non-union (14 to 50 %) in displaced fractures [3–5]. Non-union, if untreated almost inevitably leads to arthritis, usually within 5 years of injury [6, 7]. This can potentially disable patients at a relatively young age.

Recent systematic reviews [8–12] have found insufficient evidence from randomised controlled trials (RCTs) to inform clinical decisions on the treatment of scaphoid waist fractures. Eight small RCTs comparing surgery with non-operative management [12] could not establish whether patients who had surgical fixation of undisplaced or minimally displaced scaphoid fractures had better longer term outcomes. Surgery in these RCTs was shown to facilitate early return of function, but had a higher complication rate (between 9 and 22 %) compared with conservative management although the complications were usually minor [1, 13, 14]. The rate of union was similar between surgical and cast treatment with early fixation of those fractures that failed to unite [1]. A further study found similar outcomes at 10 years [15].

Despite insufficient evidence there is a rapidly increasing trend [16] for immediate surgical fixation compared to cast immobilisation for 6 weeks and fixing only those 10 to 12 % that fail to unite [1]. This current trend to fix fractures may be attributed to potential short-term benefits, but concerns remain about the lack of evidence on long-term benefits and additional risks from surgery, such as malunion, infection, implant related problems and avascular necrosis (AVN).

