### Bone union

The secondary outcome of bone union [35] is determined at 52 weeks (in line with the primary end point) using a CT scan and plain radiographs comprising posterior-anterior, lateral, semi 45° prone, semi 45°supine views and an elongated scaphoid view e.g. Ziter type view [36]. Union is defined as complete disappearance of the fracture line [3] on radiographs and complete bridging on CT scans [37–39] from those taken at baseline. We will identify partial union based on the proportion of the fracture plane traversed by bridging trabeculae on true sagittal and coronal formats of the scaphoid on CT. We are using CT to determine non-union as there is only poor to moderate inter-observer agreement (range of Kappa from 0.11 to 0.53) when determining the union of a scaphoid fracture on plain radiographs [40]. We will assess scaphoid fracture displacement on radiographs and on a CT scan [41] and determine malunion [42] on the 52 week CT scan (ratio of Scaphoid Height to Length ≥ 0.6) in the true sagittal axis of the scaphoid to assess any humpback deformity [43].

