### Complications

Expected and unexpected complications will be recorded at the 6, 12 and 52 week visit. The expected complications include:Infection, defined as for the “Surgical Site Infection” audit [52].Delayed wound healing, defined as any wound that has not healed by two weeks.Complex Regional Pain Syndrome (CRPS), defined as puffy painful swelling of the whole hand restricting full tuck of the fingers at 2 weeks.Nerve events (hypoaesthesia or numbness in the territory of the palmar cutaneous branch of the median nerve, superficial division of the radial nerve or the median nerve).Vessel events (large (>2 cm) haematoma in the line of the radial artery).Screw related complications (protrusion of either end into the adjacent joint, fracture or bending of the screw, a radiolucent halo around any part of the screw > 1 mm, screw backing out or moving).Degenerative change in the adjacent joints [53].Avascular necrosis (AVN) of the proximal pole of the scaphoid.

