### Five year clinic review

The long-term consequences of cast immobilisation and internal fixation have not been adequately determined in RCTs. Therefore, at five years after their original injury, all remaining trial participants will be asked to attend a follow-up visit at a participating hospital for a clinical and radiographic follow-up. The clinical examination will include inspection and evaluation of scar sensibility when applicable, palpation for tenderness, measurement of joint movement with a goniometer, as well as measurement of grip strength and pinch strength [15].

Participants will complete a questionnaire that asks about perceived hand problems (e.g. weakness of wrist, reduced range of movement) as well as the primary outcome measure, the PRWE, and EQ-5D.

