### Randomisation

The Research Nurse will identify potentially eligible patients presenting in Accident and Emergency (A&E) Departments, or referred from various sources (e.g. walk-in centre, cottage hospital), and at fracture clinics. The orthopaedic surgeon will confirm eligibility and invite the patient to consider joining the study. The Research Nurse or clinician will then provide an information sheet and answer any questions. The patient will be asked whether they agree to consent at that time or are offered up to 48 h to discuss the study and their participation with family or friends before deciding.

When patients have given consent their baseline forms will be completed and randomisation done. The Research Nurse or recruiting clinician will contact York Trials Unit, either by telephone or via the internet, to access the secure randomisation service. This will ensure treatment concealment and unbiased allocation. Once eligibility is confirmed, patients will be randomised (via a secure, computer generated allocation sequence) to receive immediate surgical fixation or immobilisation of the wrist in a cast.

Patients and their clinician will be informed of the allocations. As the trial is pragmatic and compares surgery with initial cast treatment, blinding of participants and clinicians to treatment allocation is not possible. When possible, the surgeon will take no part in the postoperative subjective assessment of patients. The statistical analysis will also be performed blind as far as possible. We will mitigate against bias by ensuring that all radiographs and CT scans are assessed by two independent consultant musculoskeletal radiologists and a consultant orthopaedic surgeon.

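### The modelled complication outcome is limited to clinical examination, although three of the eight listed complications are recognised wholly or largely on images (low severity)

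*Protocol article*

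**What the plan says.** The Statistical analysis plan section of the protocol article defines one modelled complication outcome: "The presence of any complication assessed by clinical examination up to 52 weeks will be analysed by logistic regression (sufficient numbers permitting"). It then classes complications as medical, surgical or related to the cast.

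The Complications section says that "Expected and unexpected complications will be recorded at the 6, 12 and 52 week visit" and lists eight expected types: infection, delayed wound healing, complex regional pain syndrome, nerve events, vessel events, screw-related complications, degenerative change in adjacent joints, and avascular necrosis of the proximal pole. One of the screw criteria is "a radiolucent halo around any part of the screw" of more than 1 mm.

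On imaging, union "is determined at 52 weeks (in line with the primary end point) using a CT scan and plain radiographs". The Randomisation section adds: "We will mitigate against bias by ensuring that all radiographs and CT scans are assessed by two independent consultant musculoskeletal radiologists", together with a consultant orthopaedic surgeon.

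**The concern.** A radiolucent halo cannot be found by examining the patient. Degenerative change and avascular necrosis are also identified mainly on radiographs or CT. The analysis rule therefore fits poorly with the protocol's own list: taken at its word, it cannot count a listed complication that shows only on an image.

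This bears on the comparison of harms. The Background section gives the reason for caution about fixation as "additional risks from surgery, such as malunion, infection, implant related problems and avascular necrosis (AVN"). Two of those four risks, implant problems and avascular necrosis, are image-recognised items on the complications list. Malunion is handled separately on the 52-week CT. The Sample size section says that surgery has to justify its exposure to risk, so a complication comparison that omits image-only implant findings would weigh harm incompletely.

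**Working it through.** The document gives no rate, power or sample size for complications, so there is no plan figure to reproduce. The check is a reading of the text plus one illustration.

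**1. Count.** Eight types are listed and three are recognised wholly or largely on images: 3/8 = 37.5%.

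**2. Meaning of clinical examination.**
- *Narrow reading.* The Five year clinic review section calls patients back "for a clinical and radiographic follow-up", which separates the two. It then says: "The clinical examination will include inspection and evaluation of scar sensibility when applicable, palpation for tenderness, measurement of joint movement with a goniometer", plus grip and pinch strength. On that usage, image-only findings fall outside the modelled outcome.
- *Loose reading.* The Complications section ties recording to the visit, and the list it refers to contains the image items. On that usage a site can record a halo it saw on a film, and the finding counts.

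**3. Where the independent readings go.** The Adverse event management section has the image reviewers tell the Chief Investigator of abnormalities. The Chief Investigator judges their importance and considers whether to log an adverse event. This is the only stated route from reader to event record. It is discretionary and it feeds adverse events, not the modelled complication outcome. The readings therefore have no fixed place in that outcome.

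**4. Who carries a screw.** Inputs: 219 per arm (Sample size); 10-12% of cast patients expected to be fixed for non-union (Table 1, Cast treatment). Assumptions: every surgical patient receives a screw, and there is no crossover or attrition.
- Cast patients with a screw: 219 × 0.10 = 21.9; 219 × 0.12 = 26.3.
- Surgical share of all patients with a screw: 219/(219 + 21.9) = 0.909; 219/(219 + 26.3) = 0.893.

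**5. Illustration under the narrow reading only.** Let f be the share of screw patients whose sole complication is an image-only screw finding, taken as equal in both arms. The document gives no value for f. With q the proportion of cast patients who have a screw, the surgery-minus-cast difference falls by f − fq = f(1 − q).

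| Assumed f | q = 0.12 | q = 0.10 |
|---|---|---|
| 1% | 0.88 points | 0.90 points |
| 10% | 8.8 points | 9.0 points |

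At f = 1% this is 219 × 0.01 = 2.2 surgical patients against 0.2-0.3 cast patients. The upper row is an outer bound and not an expectation: 10% already exceeds the lower end of the 9-22% that the Background section cites for all surgical complications together.

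**The case against.** The case against is substantial, and most of it stands.

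- The same paragraph of the plan says that all secondary outcomes will be summarised descriptively. Complications are one of them, so image findings can still be reported there. Only one regression is in question, and it is conditional on numbers.
- Sites must record related adverse events for 12 months. Screw-related complications are named among the expected ones, and adverse events are summarised by arm. This covers the only category for which a direction of bias can be argued. Avascular necrosis and degenerative change are not named in that adverse event list.
- The loose reading is plausible. Images are taken during follow-up (Table 3 notes), and the narrow meaning is borrowed from a separate five-year visit whose description need not be exhaustive.
- A test confined to clinically apparent complications can be defended. Image-only screw findings can arise only where there is a screw, and some have no clinical consequence.
- A detailed analysis plan, not shown here, may name the data source for each item.

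The last argument does not remove the point, because the protocol does more than leave detail open: it states a rule that fits badly with its own list.

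A reader might infer that image-found complications vanish from the trial's reporting, or that the surgical complication rate will be understated by a known amount. The document supports neither. The descriptive and adverse event summaries remain, and f is an assumption throughout. A reader might also infer that central reading would supply blinding. It would not, since a screw is visible on the image. What it offers is the same readers for every patient in both arms.

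**Conclusion.** The point holds at low severity. The wording of the modelled complication outcome does not match the complications list: 3 of 8 items are recognised wholly or largely on images, and read literally the regression leaves out image-only cases. For screw problems the omission falls almost wholly on the surgical arm (89-91% of patients with a screw, under the assumptions above) and would make surgery look safer. No direction is claimed for degenerative change or avascular necrosis, which can occur in either arm.

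The size cannot be taken from the document. The 0.88-0.90 points per 1% is a conversion factor that applies only under the narrow reading. Under the loose reading the loss shrinks to the extent that sites record what they see on images. The primary outcome and the sample size are unaffected.

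**What to change.** In the Statistical analysis plan section, replace the restriction to clinical examination with: *meeting a definition in the complications list and recorded at the 6, 12 or 52 week visit, whether found on examination or on imaging*. State also that unexpected complications, which the Complications section records too, still count.

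In addition, report screw-related complications, degenerative change and avascular necrosis from the independent 52-week image readings as a separate comparison by arm, with image-only findings distinguished from symptomatic ones. Week 52 is the natural point because CT and radiographs are planned then in both arms, whereas some earlier images are only those routinely collected. Keep these central findings out of the single any-complication outcome, so that silent screw findings do not raise the surgical count by construction.

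The cost is a sentence or two and a few fields on the central reading form, since the images are already taken and independently read. The drawback is that some reported image findings will have no clinical consequence, which is why they should be shown separately.

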As the non-union rate for displaced fractures is 14 % compared with 10 % for transverse undisplaced fractures [3, 5, 56], randomisation will be stratified by the presence or not of displacement of a scaphoid fracture as seen on radiographs [5, 56] Within strata, a sequence of confidential random block sizes will be used to generate the block allocation sequence. To avoid predictability of the randomisation we will not stratify by site. The radiographic views to assess displacement should include the semi 45° prone, semi 45°supine and an elongated scaphoid view e.g. Ziter [36] type view (Fig. 2). Displacement is defined as a step greater than 1 mm and less than or equal to 2 mm or a gap greater than 1 mm and less than or equal to 2 mm as seen on the radiographic views. This magnitude of displacement will avoid compromising surgeon equipoise for non-operative treatment as displacement >2 mm suggests significant instability and therefore the need for surgical intervention.

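### The union logistic regression is stated with treatment group only and omits displacement, the factor on which randomisation was stratified because of its link to non-union (minor)

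*Protocol article*

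**What the plan says.** Under Randomisation, the protocol article states that "randomisation will be stratified by the presence or not of displacement of a scaphoid fracture as seen on radiographs". The reason given is union risk: the "non-union rate for displaced fractures is 14 % compared with 10 % for transverse undisplaced fractures". Blocks are generated within these strata, and stratification by site is declined, so displacement is the only stratification factor.

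Under Statistical analysis plan, the primary PRWE model includes treatment, time, their interaction, and terms "adjusting for age, fracture displacement (undisplaced vs. minimally displaced) and hand dominance". The PRWE subscales, SF-12 component summaries, range and grip strength are then "analysed using the same methods as the primary analysis adjusting for the same covariates". Union is not in that list and has its own sentences: "Union will be dichotomised into a ‘Probably need surgery’ group" (0 to 20% union) and its complement (over 20%), and this binary outcome is "analysed using a logistic regression adjusting for treatment group". Nothing elsewhere in the article adds displacement to the union model. The displacement subgroup analysis is attached to the primary PRWE model.

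**The concern.** The protocol stratifies on displacement because of non-union, and then adjusts for displacement in its models for patient-reported scores, movement and strength but not in its model for union. This is not a detail left to a later analysis plan, because the sentence states what the union model contains.

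Two consequences follow.

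- **Precision.** Blocking within strata removes between-stratum variation from the treatment comparison. A model without the stratum still counts that variation as noise, so its standard error is too large and its test conservative.
- **Estimand.** The odds ratio is non-collapsible. When the stratum is prognostic and there is a treatment effect, the odds ratio without the stratum is marginal and lies closer to 1 than the one conditional on displacement. The protocol does not say that the marginal version was chosen on purpose, and its other models are all conditional on displacement.

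**Working it through.** **The plan's own figure.** The article gives no power calculation for union. The only stated sample size is for PRWE (difference 6, SD 20, two-sided 5%, 80% power). It reproduces: 175 per arm, 350 in total, and 350 / (1 − 0.20) = 437.5, rounded up to 438. I use 175 per arm as the assumed number analysed for union.

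**Inputs**
- Non-union risk by stratum: 14% displaced and 10% undisplaced (Randomisation).
- Displaced share w: not stated; assumed 20%, 35% and 50%.
- Treatment odds ratio for union: not stated; assumed 1 (null), and 0.5 or its inverse 2 for illustration.

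**Step 1. How prognostic is displacement?** The share of outcome variance between strata is R = w(1 − w)(p_d − p_u)² / [p(1 − p)], where p is the overall risk.
- w = 0.20: p = 0.108; R = 0.16 × 0.0016 / (0.108 × 0.892) = 0.0027.
- w = 0.35: p = 0.114; R = 0.2275 × 0.0016 / (0.114 × 0.886) = 0.0036.
- w = 0.50: p = 0.120; R = 0.25 × 0.0016 / (0.120 × 0.880) = 0.0038.

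Displacement thus accounts for 0.3% to 0.4% of the variance.

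**Step 2. Type I error without the stratum.** Under the null, the model's variance of the log odds ratio exceeds the true variance under stratified randomisation by the factor 1 / (1 − R). The actual level is 2[1 − Φ(1.96 × √(1 / (1 − R)))].
- w = 0.20: factor 1.0027, level 0.0497.
- w = 0.35: factor 1.0036, level 0.0496.
- w = 0.50: factor 1.0038, level 0.0496.

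**Step 3. Marginal against conditional odds ratio.** Take w = 0.35, conditional odds ratio 0.5, and control risks 0.14 and 0.10.
- Treated risks: 0.14/0.86 × 0.5 = 0.0814 in odds, so 0.0753; 0.10/0.90 × 0.5 = 0.0556 in odds, so 0.0526.
- Overall risks: control 0.35 × 0.14 + 0.65 × 0.10 = 0.1140; treated 0.35 × 0.0753 + 0.65 × 0.0526 = 0.0606.
- Marginal odds ratio: (0.0606/0.9394) / (0.1140/0.8860) = 0.501. Inverted, 2.00 becomes 1.996.

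The same calculation at w = 0.20 and 0.50 gives 0.501 in each case (inverted, 1.997 and 1.996). Applying an odds ratio of 2 upwards from the same control risks gives 1.995, 1.994 and 1.993 for the three shares. The range is therefore about 1.99 to 2.00.

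**Step 4. Power at odds ratio 0.5.** Large-sample power without and with the stratum:
- w = 0.20: 0.398 and 0.399.
- w = 0.35: 0.415 and 0.416.
- w = 0.50: 0.431 and 0.432.

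The loss is about 0.1 percentage point.

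**The case against.** The strongest reply is that the omission does almost no harm. Stratified randomisation balances displacement by design, the test errs on the safe side, the marginal odds ratio is a valid effect and not a biased one, and union is secondary to a PRWE model that does adjust. All of this stands and is why the point is minor.

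A reader might infer a larger effect from the Background, which describes cast treatment "with a higher incidence of non-union (14 to 50 %) in displaced fractures", and put the upper part of that range into the calculation. The documents do not support this. That range is for displaced fractures in general, whereas this trial excludes displacement over 2 mm and its displaced stratum is a step or gap above 1 mm and up to 2 mm. For the stratification factor itself the protocol uses 14%.

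Even 10% and 14% may be too high for this outcome. They are background non-union rates. Union here is assessed at 52 weeks, after fixation of cast treatments that failed, half the patients have immediate surgery, and the modelled event is union of 20% or less. If the undisplaced risk were, for illustration, 1% to 3% with the same 1.4 ratio between strata, R would be at most about 0.1% and an odds ratio of 2.00 would become about 1.998. Events would also be scarce: 350 × 0.01 = 3.5 to 350 × 0.03 = 10.5. An extra term is then not entirely free.

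A reader might also extend the point to the complications model. There the article names a logistic regression and no covariate set. That is silence which a fuller plan may fill, and the stated reason for stratifying concerns non-union, so no finding arises.

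Finally, the wording may be loose shorthand, since treatment is the effect being estimated and not an adjustment. But union sits outside the list of outcomes sharing the primary covariates, so treatment alone is the natural reading.

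**Conclusion.** The point holds as a minor inconsistency in the stated union model. The protocol stratifies on displacement because of non-union and leaves it out of the model for union, while keeping it in the other models whose covariates it lists.

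At the protocol's 10% versus 14%, the cost is a type I error of about 0.0497 in place of 0.05, a power loss of about 0.1 percentage point, and an odds ratio of about 1.99 to 2.00 in place of 2.00. These figures rest on 175 analysed per arm, a displaced share of 20% to 50%, and assumed treatment odds ratios of 0.5 or 2. The effect would grow only if displacement were much more prognostic in the enrolled population, which nothing in the article shows. There is no inflation of type I error, no bias in the marginal odds ratio, and no consequence for the primary analysis or the sample size.

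**What to change.** State the union model as a logistic regression on treatment group and displacement stratum, using the stratum as recorded at randomisation. Specify in advance that a penalised (Firth) or stratified exact fit will be used if 52-week events are few. If a marginal odds ratio is wanted instead, say so and give the reason for leaving displacement out.

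The cost is one sentence in the plan and one extra parameter, which is a small drawback if events are sparse. No new data are needed, because displacement is known for every randomised participant. Fixing the covariate now also removes a later choice between adjusted and unadjusted union results.
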